**Fig. 1 Fig1:**
[figure not shown]
MAPS flow chart

#### Peer navigator training and supervision

We will recruit 4 peer navigators (3 males, 1 female) and train them to fidelity to deliver the intervention. The 4 half-day long, didactic in-person initial trainings will consist of reviewing the peer navigation intervention rationale, materials, and strategies; audio-taped demonstrations; and live practice sessions with feedback. Weekly group supervision meetings will be held with peer navigators via phone or in-person to assist with any outstanding concerns. All peer navigation sessions will be audiotaped. Supervision will involve review of peer navigators’ audiotaped sessions (with fidelity rating as appropriate), group supervision and case discussion, and individual phone consultation as needed.

We will employ several approaches that we have found helpful in achieving low attrition rates (0–20%) in previous intervention studies with individuals re-entering the community after incarceration [28–31] (including those who were homeless) and other high-risk samples [32, 33]. These include study staff’s strong relationships with participants and efforts to value and appreciate their study participation. The study research assistant will call participants and mail them letters to remind them of their appointments and maintain a list of 2 other people who will always know where participants reside. Locator information will be updated at each study contact. Telephone follow-up assessment (removing the need for transportation) and study team flexibility in scheduling follow-up assessments (i.e., on evenings or weekends) will also facilitate participant retention. Finally, participants will be remunerated $50 for each follow-up assessment, facilitating retention.

#### Fidelity ratings

We will develop intervention adherence and competence ratings based on the intervention manual. Adherence rating scales will consist of checklists of tasks to be completed at each meeting. Competence rating scales will reflect peer navigator general skills, such as reflective listening skills, engaging people through goal setting, using a strength-based approach, and advocacy. We will use these scales to rate a randomly selected 33% of the open trial tapes. Scale development will continue until the item content is satisfactory, and interrater reliability is acceptable (> .80).

#### Assessments

##### Primary outcomes: feasibility and acceptability

The primary outcomes of this study will be to evaluate the *feasibility* and *acceptability* of the proposed recruitment methods and research design, of the intervention training methods, of delivering the enhanced peer-navigator and control interventions. We will use the End of Treatment Questionnaire [20] to assess client experience with the intervention. To measure the feasibility, acceptability and satisfaction with the intervention, we will use the Client Satisfaction Questionnaire (CSQ-8) [34]. We will also evaluate the recruitment, refusal, retention, attendance rates.

##### Secondary outcomes

**Clinical outcomes**

The presence and severity of manic symptoms will be measured by using the Altman Self-Rating Mania Scale (ASRM) [35]. This 5-item scale has been reported to be consistent with standard DSM 5 diagnosis of presence and severity of manic symptoms [35]. We will use the 16-item version of Prodromal Questionnaire (PQ-16) to assess psychotic symptoms [36] and the Quick Inventory of Depressive Symptoms (QIDS-SR) [37] to assess depressive symptoms. The 12-item WHO-Disability Assessment Schedule (WHODAS-II) [38] will be used to measure functioning in the domains of cognition, mobility, self-care, getting along/interaction with other people, life activities, and participation in community activities. The 4-item Brief Adherence Rating Scale (BARS) [39] will be used to assess adherence to psychiatric medications. BARS items evaluate past month adherence in terms of the number of prescribed doses per day, number of days the patient did not take the prescribed doses, and number of days the client took less than the prescribed doses. We will use Treatment History Interview (THI) [40] to measure number of hospitalizations after release. Numbers of suicide attempts will be measured by using the Columbia Suicide Severity Rating Scale (C-SSRS) [41]. Substance use will be measured using the Alcohol Use Disorders Identification Test (AUDIT) [42] and Drug Use Disorders Identification Test (DUDIT) [43] and brief measures of alcohol and drug use severity. The AUDIT has been recommended as part of the NIH PhenX Toolkit of assessments.

**Life context outcomes**

We will use a calendar-based interview method [44–50] to measure number of nights unstably housed and days until rearrest.

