No peer support interventions have been tested to assist with mental health service linkage for individuals with SMI during re-entry to the community after jail incarceration. One study of substance use peer navigators during community re-entry (not among individuals with SMI) has shown that using a peer navigator model during re-entry is feasible [5]. The purpose of the proposed study is to develop a peer navigator intervention for mental health, substance use, and medical care treatment engagement among justice-involved individuals with SMI who are re-entering the community after jail incarceration and to then evaluate its feasibility, acceptability, and ways the intervention contributed to the desired outcomes.

In this study, peer navigators will be trained individuals who share the joint experience of having the diagnosis of SMI and also having a history of justice involvement. Their lived experience as someone diagnosed with SMI and familiarity with the justice system makes them ideal practical supports for facilitating prompt and ongoing access to mental health, medical care, and substance use services for others at community re-entry.

This pilot study will provide formative work for a larger randomized controlled trial evaluating the effectiveness of peer navigator intervention for justice-involved individuals with SMI. The study will have two phases. The first (development) phase aims to (1) enhance and tailor a peer-navigator intervention for justice-involved individuals with SMI re-entering the community using qualitative research; (2) develop, implement, and evaluate the intervention training program using qualitative and quantitative techniques; and (3) improve the clarity, content, acceptability, and feasibility of the tailored peer navigator intervention through a small open trial (*n* = 15) of justice-involved individuals with SMI re-entering the community. The second (pilot study) phase aims to conduct a randomized pilot trial in a sample of 40 justice-involved individuals with SMI who are anticipating jail release in the next 30 days. The control condition will be Standard of Care (SOC). Study assessments will take place at baseline, 3 months, and 6 months after release. The goal is to demonstrate the feasibility and acceptability of the proposed recruitment methods and research design, of the intervention training methods, and of delivering the enhanced peer-navigator and control interventions.

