##### Demographic/screening measures

Demographic/screening measures will include age, educational level, marital status, occupation, employment (status, number of hours per week), income, race, type of offense for which currently incarcerated, number of prior arrests, number of prior convictions, and length of sentence. These data will be compared to jail records. At follow-ups, occupation, employment (status, number of hours per week), and income will be repeated. We will use the Structured Clinical Interview for DSM-5 (SCID) [21] to ensure that all study participants have DSM-5 diagnosis of SMI, as operationalized in our inclusion criteria. The SCID is a semi-structured interview guide used for diagnosis of SMI. The 90-item Symptom Checklist 90 (SCL-90) [54] will be used to establish the eligibility criterion of “currently symptomatic” (using the SCL-90 score clinical cutoff of ≥25) [55]. Table 3 summarizes measurements and timepoints.

**Table 3 Tab3:** Measurements and timepoints

Construct	Measure	Baseline/pre-release	3 months after release	6 months after release
Demographic and inclusion				
Demographics	Demographics	X		
Inclusion	SCID [21] and SCL-90 [54]	X		
Feasibility and acceptability				
Feasibility and acceptability	CSQ-8; ETQ; WAI			X
Health service outcomes				
Mental health tx utilization	THI	X	X	X
Substance use tx utilization		X	X	X
Medical tx utilization		X	X	X
Days to first contact with a provider			X	X
Clinical outcomes				
Mental health symptoms	ASRM [35]; PQ-16 [36]; QIDS	X	X	X
Functioning	WHODAS-12 [38]	X	X	X
Psychiatric medication adherence	BARS [39]	X	X	X
Psychiatric hospitalizations	THI	X	X	X
Suicide attempts	C-SSRS [41]	X	X	X
Substance use	AUDIT/DUDIT	X	X	X
Nights unstably housed, time to rearrest	Calendar-based interview	X	X	X
Target mechanisms				
Informational support for treatment	PROMIS [51]	X	X	X
Instrumental support for treatment	PROMIS [51]	X	X	X
Emotional support for treatment	IPA [52]	X	X	X
Social norms re: treatment and recovery	SSMI-SF [53]	X	X	X

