**Secondary outcomes**

We will (1) calculate the effect size and 95% CI for number of outpatient mental health appointments. Exploratory tests for differences between conditions will use mixed linear models, with number of outpatient mental health appointments in the 90 days prior to incarceration and baseline committed partnership status as a covariate. (2) Calculate the effect size and 95% CI separately for number of outpatient substance use appointments and number of outpatient medical appointments. (3) Conduct an exploratory comparison of the number of days between jail release and the first outpatient mental health appointment using Cox regression.

We will separately calculate the effect size and 95% CI for secondary outcomes, including mental health symptoms (ASRM, PQ-16, and QIDS-SR scores), functioning (WHODAS-12 score), psychiatric medication adherence (BARS score), number of post-release hospitalizations (from the THI), substance use (AUDIT and DUDIT scores), and nights unstably housed. Separate exploratory tests for differences between conditions will use mixed linear models, with baseline scores as covariates. We will conduct an exploratory comparison of time until rearrest using Cox regression.

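### Time to rearrest comes only from an interview that rearrest can prevent, so censoring is likely to be informative; partner jail records should be added as a second source

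*Protocol article*

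**What the plan says.** - **Source.** Under Life context outcomes, a calendar-based interview is used "to measure number of nights unstably housed and days until rearrest". Table 3 lists "Nights unstably housed, time to rearrest" with the calendar-based interview as its only measure, at baseline, 3 and 6 months.
- **Timing.** Under Background: "Study assessments will take place at baseline, 3 months, and 6 months after release".
- **Mode.** Under Peer navigator training and supervision, one listed retention aid is "Telephone follow-up assessment (removing the need for transportation"). Follow-up interviews in custody are not mentioned.
- **Analysis.** Under Secondary outcomes in Data analysis: "We will conduct an exploratory comparison of time until rearrest using Cox regression".
- **Records already in use.** Under Demographic/screening measures, after a list that includes prior arrests and convictions: "These data will be compared to jail records". Study design and setting names the county sheriff's office as a partner.

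**The concern.** The event being measured can stop the measurement. Someone who has been rearrested may be in custody when the interview is due. The retention tools described (reminder calls, mailed letters, telephone assessment, evening or weekend scheduling) suit people living in the community. If such a person is not interviewed again, the rearrest is never seen and the person leaves the analysis looking event-free. Cox regression assumes that censoring carries no information about the event. The article's remark that mixed linear models accommodate missing data does not help, because this outcome is not analysed by a mixed model.

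Two things are at stake. The rearrest rate, which a later trial would use for planning, would be too low. The comparison between arms could also be distorted if rearrested participants are easier to find in one arm. That is plausible, since only MAPS participants have a navigator in regular contact after release. The article says its main interest is in the direction and range of effects, and distortion between arms would damage exactly that.

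The plan checks self-reported arrest history against jail records at baseline, but names no such check once arrest becomes an outcome.

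**Working it through.** **1. The plan's own figure.** The article gives power .80 for d = .91 with about 20 per arm and alpha .05. A two-sided two-sample t-test (noncentral t) gives 0.801, so it reproduces. No figure is given for rearrest. Every rearrest rate and loss rate below is therefore an assumption.

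**2. One group, true 6-month rearrest 30%.** Rearrest times were simulated as exponential. Each interview looks back to release, so a missed 3-month visit can be recovered at 6 months. Follow-up ends at the last completed interview.

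| Missed per visit: rearrested / others | Kaplan-Meier estimate at 6 months |
|---|---|
| 10% / 10% | 30% |
| 30% / 10% | 26.5% |
| 50% / 10% | 21.5% |
| 80% / 10% | 10.6% |

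If only people still in jail on the visit date are hard to reach (mean stay 1 to 2 months, 50–80% of them missed), the estimate is 24–28%.

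**3. Two arms, true hazard ratio 1, true 6-month rearrest 40% in both.** Let q be the chance that an already rearrested person misses a visit. Others miss with probability 0.10.

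- Hazard: λ = −ln(0.6)/6 = 0.0851 per month.
- Rearrest in months 0–3: a = 1 − √0.6 = 0.2254. In months 3–6: b = √0.6 − 0.6 = 0.1746.
- Events seen: E(q) = a(1 − q²) + b(1 − q).
  - E(0.3) = 0.2254 × 0.91 + 0.1746 × 0.70 = 0.327
  - E(0.6) = 0.2254 × 0.64 + 0.1746 × 0.40 = 0.214
- Months at risk up to rearrest: a/λ − 3√0.6 = 0.324 for the early rearrests, and 0.4/λ − 3.6 − 0.324 = 0.774 for the later ones.
- Person-months seen: T(q) = 0.324(1 − q²) + 0.774(1 − q) + 3 × 0.90 × b × q + 0.6 × (0.90 × 6 + 0.10 × 0.90 × 3).
  - T(0.3) = 0.295 + 0.542 + 0.141 + 3.402 = 4.380
  - T(0.6) = 0.207 + 0.310 + 0.283 + 3.402 = 4.202
- Observed rates: 0.327/4.380 = 0.0747 and 0.214/4.202 = 0.0510.
- **Observed rate ratio: about 1.5 if MAPS has the smaller loss (0.0747/0.0510), and about 0.7 if it has the larger.** Simulation gives 1.46 and 0.69.
- Check with q = 0.10 for everyone: E = 0.380, T = 4.467, rate 0.0851 = λ, so no bias.
- Equal loss among the rearrested in both arms (50% or 80%): simulated ratios 1.00 and 0.98.

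The loss of 60% implies 6-month attrition of 0.4 × 0.6 + 0.6 × 0.1 = 30% in that arm, above the 0–20% cited from earlier studies. The other arm has 0.4 × 0.3 + 0.6 × 0.1 = 18%.

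**4. A case inside the cited attrition range.** Again 40% rearrested in both arms. Assume loss of 45% of the rearrested under standard of care, 20% of the rearrested under MAPS, and 3% of everyone else.

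- Overall loss: 0.4 × 0.45 + 0.6 × 0.03 = 19.8%, and 0.4 × 0.20 + 0.6 × 0.03 = 9.8%.
- Rearrested among those interviewed: 0.22/(0.22 + 0.582) = 27% under standard of care, and 0.32/(0.32 + 0.582) = 36% under MAPS.

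These are crude proportions, not the planned Cox analysis. They show that retention within the cited range does not exclude a false difference of about 8 points.

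**5. Precision.** By Schoenfeld's formula, power = Φ(|ln HR| × √(D/4) − 1.96). For HR 0.5, D = 8 events gives Φ(0.98 − 1.96) = 16%, and D = 20 gives Φ(1.55 − 1.96) = 34%. The 8-point gap in step 4 is about half a standard error (about 16 points with roughly 16 and 18 people interviewed).

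**The case against.** The article does not say that rearrested people are hard to interview. A reader might infer that they are the least obtainable group, that follow-up is largely by telephone, or that censoring is known to be informative. None of this is stated. Telephone assessment is one item in a list of retention aids, with no share given. The research team works inside the partner jail, so someone held there again might be easier to find than someone unstably housed. Two locator persons are required at entry, locator details are updated at each contact, each follow-up is paid, and earlier re-entry studies by the team had 0–20% attrition. The interview looks back, so one missed visit need not lose the event.

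Differential loss by arm is also an inference. Navigators have no role in assessments, and retention work falls to the research assistant without distinction by arm. Equal loss hardly moves the hazard ratio.

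These objections stand as limits on how firmly the point can be put, and they rule out a definite size. They do not remove it. No interview in custody is planned, the cited attrition is not split by rearrest, and step 2 already allows a missed visit to be recovered. A censoring rule may well be in the full protocol or analysis plan, and its absence here is not the complaint. The complaint is the stated choice of a single source.

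The exploratory status and low power are real and lower the priority. They do not make a biased direction harmless in a pilot meant to show direction.

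**Conclusion.** The point holds as a likely, not a demonstrated, bias. With interview as the only source, censoring of time to rearrest is likely to be informative and the rearrest rate is likely to be understated. The hazard ratio is at risk only if loss among the rearrested differs by arm, and then in either direction. The size cannot be taken from the article. Under the stated assumptions it runs from nothing, when missingness is unrelated to rearrest, to an observed rate ratio of about 0.7 or 1.5 at a true hazard ratio of 1.

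A reader might go further and conclude that jail records should replace the interview. The documents do not support that. They show one county jail's records, used at baseline only, and such records would miss arrests elsewhere. The records belong beside the interview.

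Priority is minor to moderate: an exploratory secondary outcome in a 40-person feasibility pilot, but with a cheap remedy through an existing partner.

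**What to change.** - **Life context outcomes and Table 3:** add partner jail records through 6 months after release, for all randomised participants and with their consent, as a second source beside the calendar interview. Take the earliest rearrest date from either source.
- **Secondary outcomes, Data analysis:** run the Cox comparison on the combined source. Censor people without an event at 6 months, or at the record-search date if that is earlier. Repeat it as a sensitivity analysis with un-interviewed people without a recorded rearrest censored at last contact. This second run is needed because the main one treats an un-interviewed person arrested outside the county as event-free.

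The cost is one record pull and a sentence in the consent form and data-use agreement, on the assumption that the access used at baseline can be extended to follow-up. The sentence has to be in place before participants consent. Arrests outside the county would still be seen only by interview.

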**Target mechanisms**

Measuring the target mechanisms for this peer navigation intervention may contribute toward refining the intervention, clarifying the peer navigator roles, and improving client outcomes. Instrumental support and informational support for treatment engagement will be measured using an adapted version of the Patient-Reported Outcomes Measurement Information System (PROMIS) measures, originally developed for people with chronic illness [51]. We will adapt the informational support (10 items) and instrumental support (5 items) sub-sections of the scale to assess the frequency and ease of obtaining these supports when needed. Emotional support for treatment engagement will be assessed using items from the Important People and Activities Scale [52]. The Self Stigma of Mental Illness Short Form (SSMI-SF) will be used to assess social norms around treatment engagement and recovery [53] (Table 2).

**Table 2 Tab2:** Secondary outcomes of MAPS study

Health service outcomes	Utilization of community mental health (primary), medical, and substance use services; fewer days between release from jail and first contact with any health care provider.
Clinical outcomes	Reduced psychiatric symptoms, increased functioning, adherence to psychiatric medications, fewer substance using days, fewer hospitalizations, and suicide attempts.
Life context outcomes	Nights unstably housed and time until rearrest.
Potential target mechanisms	Instrumental (primary), informational, and emotional support for treatment engagement and social norms about treatment engagement and recovery.

##### Demographic/screening measures

Demographic/screening measures will include age, educational level, marital status, occupation, employment (status, number of hours per week), income, race, type of offense for which currently incarcerated, number of prior arrests, number of prior convictions, and length of sentence. These data will be compared to jail records. At follow-ups, occupation, employment (status, number of hours per week), and income will be repeated. We will use the Structured Clinical Interview for DSM-5 (SCID) [21] to ensure that all study participants have DSM-5 diagnosis of SMI, as operationalized in our inclusion criteria. The SCID is a semi-structured interview guide used for diagnosis of SMI. The 90-item Symptom Checklist 90 (SCL-90) [54] will be used to establish the eligibility criterion of “currently symptomatic” (using the SCL-90 score clinical cutoff of ≥25) [55]. Table 3 summarizes measurements and timepoints.

**Table 3 Tab3:** Measurements and timepoints

Construct	Measure	Baseline/pre-release	3 months after release	6 months after release
Demographic and inclusion				
Demographics	Demographics	X		
Inclusion	SCID [21] and SCL-90 [54]	X		
Feasibility and acceptability				
Feasibility and acceptability	CSQ-8; ETQ; WAI			X
Health service outcomes				
Mental health tx utilization	THI	X	X	X
Substance use tx utilization		X	X	X
Medical tx utilization		X	X	X
Days to first contact with a provider			X	X
Clinical outcomes				
Mental health symptoms	ASRM [35]; PQ-16 [36]; QIDS	X	X	X
Functioning	WHODAS-12 [38]	X	X	X
Psychiatric medication adherence	BARS [39]	X	X	X
Psychiatric hospitalizations	THI	X	X	X
Suicide attempts	C-SSRS [41]	X	X	X
Substance use	AUDIT/DUDIT	X	X	X
Nights unstably housed, time to rearrest	Calendar-based interview	X	X	X
Target mechanisms				
Informational support for treatment	PROMIS [51]	X	X	X
Instrumental support for treatment	PROMIS [51]	X	X	X
Emotional support for treatment	IPA [52]	X	X	X
Social norms re: treatment and recovery	SSMI-SF [53]	X	X	X

#### Data analysis

The purpose of the R34 Exploratory Research Award is to collect preliminary data to assess feasibility and acceptability of an intervention and to inform a subsequent fully powered randomized clinical trial. With data from 40 participants in intent to treat analyses (about 20 per condition), we would only have statistical power adequate (.80) to detect large effects (*d* = .91) with alpha of .05. Randomized trials of SMI interventions rarely produce effect sizes this large; therefore, our primary emphasis will be on examining the direction of effects and the range of effect sizes for differences between conditions. This pilot data can be used to demonstrate whether the effects of treatment look promising across a set of outcome variables, to begin to examine distribution of outcome variables to inform future analytic strategies.

Primary analyses will be intent-to-treat (using data from all treatment enrollees). We will also conduct secondary dose-response analyses. Analysis strategies used (mixed linear models) can accommodate missing data and can be used in a sample of 40 with a simple model. We will use the STATA quantitative data analysis software [56].

